### Recruitment and screening

2.4

Participants will be recruited through advertising the study on radio stations and in newspapers, at health centres and healthcare plans, on posters and pamphlets and via institutional e‐mail and social media promotions, which will contain electronic links and contact information for the research team. When contacted by e‐mail or telephone, some questions will be asked to determine whether individuals meet the inclusion criteria. Then, they will be invited to a first visit at the Laboratory of Energy Metabolism and Body Composition of the Universidade Federal de Viçosa to confirm eligibility through the application of an in‐person screening questionnaire supplemented by information obtained in the previous screening, measurement of anthropometric measurements (weight, height and waist circumference) and blood pressure and biochemical tests (glucose, total cholesterol and fractions, triglycerides) from the last 3 months presented by the volunteer (when available) or solicited by the research team's. After confirming eligibility, the participant will be informed about the study procedures. If they agree, they must then sign the Informed Consent form. Following confirmation of participation in the study, a DNA sample will be collected for genotyping and determination of the genetic score.

### Genetic score

2.5

To perform the genetic tests (SNPs panel—*FTO*: rs9939609 and rs1121980; *MC4R*: rs17782313; *LEP*: rs7799039), four previously well‐studied genetic variants associated with obesity and appetite regulation were selected. The swab technique will be used to collect cells from the oral mucosa. Participants will be instructed to rinse their mouths with 100 mL of distilled water previously, and the collection will be performed by scraping the inside of the cheeks with small sterile cytological brushes, making circular movements approximately 30 times. Then, the brushes will have the external portion of the stems cut and placed in 2 mL microtubes. The collected samples will be stored in an ultra‐low freezer at −80°C and analysed by real‐time polymerase chain reaction (PCR). The score will be assessed based on the presence or absence of the evaluated SNPs, and classification will be determined by the number of variant risk alleles at the Laboratory of Clinical Analysis and Genomics (UFV).

### Outcomes

2.6

The primary clinical outcome will be estimated weight loss of 5%–10% of initial body weight, resulting in corresponding changes in BMI, waist circumference and body composition. Secondary outcomes will include improvements in indicators of quality of life, self‐esteem and quality of food intake, as well as serum cardiometabolic, oxy‐inflammatory, epigenetic, satiety and intestinal permeability markers.

### Sample size calculation

2.7

For a sample calculation, analyses were performed assuming a weight loss of 5%–10% as the primary outcome, a significance level of 5%, a test power of 90% and an effect size of 0.50. Thus, considering a 30% sample loss, the sample size is 30 per group, totalling 120 participants. The G*Power 3.0.10 analysis programme was used, adopting an ‘a priori’ analysis using the variance test (ANOVA) for repeated measures.

### Randomisation and allocation

2.8

Based on the genotypes, an unweighted risk genetic will be calculated, obtained by summing the number of identified risk alleles. Each genotype will be coded as 0, 1 or 2, according to the absence, presence in heterozygosity or homozygosity of the risk allele, resulting in a total genetic risk scoring (GRS) ranging from 0 to 8. From there, a sum of risk alleles will be made, and it will be pre‐categorised as high (≥3 variant risk alleles) or low (<3 variant risk alleles).^18^

Randomisation will be performed using the MinimPy® software (version 3.0), employing the minimisation method to ensure balance among the four groups in terms of sex, risk genetic (LR and HR), age range (20–39 years; 40–55 years) and BMI range (27.0–29.9 kg/m^2^; 30.0–34.9 kg/m^2^; 35.0–40.0 kg/m^2^).

### Estimate of the energy requirements

2.9

The resting energy expenditure (REE) of all participants will be estimated using the Mifflin‐St. Jeor equation^19^ using the current body weight for the calculation. Then, the total energy expenditure will be determined by multiplying the REE by the individual's physical activity level. Caloric restriction will be defined by subtracting 500 kcal from each participant's estimated daily energy requirement.^14^, ^16^

### Control group

2.10

The control group will receive a balanced diet with a macronutrient distribution and a caloric restriction of 500 kcal/day. Macronutrient distributions were determined according to guidelines for the treatment of overweight and obesity, which do not account for the individual's genotype.^14^, ^15^ The menus will be divided into six meals/day (breakfast, morning snack, lunch, afternoon snack, dinner and evening snack). They will be composed exclusively of foods with a lower degree of processing (whole foods, culinary ingredients and minimally processed foods).^20^ The menus will be calculated using an Excel spreadsheet based on the Nutritional Composition Tables of Foods Consumed in Brazil.^21^ Besides, participants will be instructed to drink at least 2 L of water/day and to avoid consuming oats, seeds and cashews throughout the study period.

### Intervention group and satiety protocol

2.11

The intervention group will receive 500 kcal/day caloric restriction and a personalised diet designed to control satiety. The distribution of macronutrients was designed based on previous studies that investigated the effect of diets with different macronutrient distributions on body weight, metabolic markers and satiety sensation in individuals carrying genetic polymorphisms in the FTO, MC4R and LEP genes.^22^, ^23^, ^24^

The menus will follow exactly the same preparation and division criteria used for the control group. In addition to calorie‐restricted meal plans, an additional protocol focused on promoting satiety (satiety protocol) will be adopted, which consists of the following strategies: high‐protein breakfast (20% of the meal's calories coming from protein), daily consumption of a standardised granola (either a sweet or a salty version), meal frequency, mastication techniques and meal duration. The protocol as a whole was developed to act on both mechanical mechanisms and hormonal signalling pathways related to satiety. All strategies adopted were based on evidence from previous studies^25^, ^26^, ^27^ that demonstrated the effect of certain nutrients and foods on the modulation of satiety, including their influence on mechanical and hormonal processes and the subjective perception of satiety.

Participants will be instructed to consume the granola sachet daily at the most appropriate time for each one, which can be divided into two portions per day. The calories of the granola will be accounted within of the calculation of the caloric‐restricted diet. Granola will be used as a strategy to provide additional fibre and monounsaturated fats, as well as to stimulate mastication. Each serving of granola consist of 30 g of oats, 24 g of seeds, 15 g of cashew nuts and 5 g of cashew oil. Two flavours of granola will be developed: (1) sweet: with an additional of 5 g of brown sugar and 10 g of black raisins and (2) salty: with an additional of 0.15 g of salt and 0.3 g of sweet paprika.

The overview of the recommendations for the control and intervention groups is presented in Table 1.

**TABLE 1 dom70414-tbl-0001:** Overview of the GenOn Programme dietary intervention.

Outcomes	Control group	Satiety group
Calorie requirement	−500 kcal/day from energy requirement^20^	−500 kcal/day from energy requirement^20^
Dietary protein intake	15%–20% of energy^14^, ^15^	20%–25% of energy^14^, ^15^
Breakfast protein intake	10% of the daily protein intake^14^, ^15^	20% of the daily protein intake^24^, ^25^
Dietary carbohydrate intake	50%–60% of energy^14^, ^15^	45%–50% of energy^14^, ^15^
Dietary fibre intake	≤25 g/day^14^, ^15^	>30–35 g/day^14^, ^15^
Dietary fat intake	25%–30% of energy^14^, ^15^	25%–30% of energy^14^, ^15^
Dietary saturated fat intake	<10% of energy^14^, ^15^	<10% of energy^14^, ^15^
Dietary monounsaturated fat intake	<10% of energy^14^, ^15^	<10%–15% of energy^14^, ^15^
Dietary polyunsaturated fat intake	<8% of energy^14^, ^15^	<10% of energy^14^, ^15^
Intake of standardised granola (sweet or salty version)	Avoid consuming granola, oats, pumpkin, sunflower, flax and sesame seeds	Daily consumption of one sachet (30 g), which can be divided into two portions per day
Cashew nuts	Avoid consuming nuts	15 g/day
Individual consultations	Activities for the treatment of overweight and obesity	Activities for the treatment of overweight and obesity and techniques for the control of hunger and satiety

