### Monitoring and adherence to study protocol

2.13

Adherence to the protocol (in both the control and intervention groups) will be monitored through seven nutritional counselling consultations conducted biweekly during the first 2 months and subsequently monthly until the completion of the 18‐week study. The consultations will be conducted in person or via video conference, during which the consumption of granola, any possible adverse events, and the introduction or changes in usual medication doses for acute or continuous use will be recorded, and nutritional guidelines will be reinforced. In addition, during individual dietary consultations, adherence to granola consumption will be assessed by counting the returned empty packaging.

The control groups will also attend the monitoring visits and will undergo the same assessments as the intervention groups. During the study period, participants who do not adhere to the eating plan (in both the control and intervention groups), do not have good adherence to the satiety protocol (absence of consumption of the granola and intake of the high‐protein breakfast on at least five consecutive days), have a frequency of less than 75% in the activities of the collective intervention and nutritional consultations, or who experience any non‐transient adverse event and gastrointestinal symptoms that compromise health or quality of life related to the consumption of granola, will be discontinued from the study.

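### Section 2.11 and Table 1 give different daily granola amounts (74–89 g against 30 g), so the energy to be counted in the satiety arm's restricted diet is not fixed; the high-protein breakfast is also defined in two ways

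*Protocol article*

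**What the plan says.** **Granola.** Section 2.11 (Intervention group and satiety protocol) gives the recipe for each serving: "30 g of oats, 24 g of seeds, 15 g of cashew nuts and 5 g of cashew oil". The sweet version has "an additional of 5 g of brown sugar and 10 g of black raisins"; the salty version has "an additional of 0.15 g of salt and 0.3 g of sweet paprika". Participants eat a sachet every day, and its calories are counted inside the calorie-restricted diet. Table 1, satiety group, gives the amount as "Daily consumption of one sachet (30 g), which can be divided into two portions per day". A separate Table 1 row sets cashew nuts at 15 g/day for the same group.

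**Breakfast.** Section 2.11 defines the high-protein breakfast by the share of that meal's calories that comes from protein, namely 20%. Table 1 defines it for the satiety group as "20% of the daily protein intake", against 10% for control. Table 1 sets all-day protein in the satiety group at 20–25% of energy.

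**Where these are used.** Both arms are specified at 500 kcal/day below requirement (section 2.9 and Table 1). Section 2.13 discontinues participants for poor adherence to the satiety protocol, described as "absence of consumption of the granola and intake of the" high-protein breakfast over at least five consecutive days. Granola adherence is checked by counting returned empty packages.

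**The concern.** Granola is the one product given only to the test arm, and its daily amount appears as two figures that differ by a factor of 2.5 to 3. The design holds energy restriction equal between arms and varies the satiety strategy. That equality depends on the menu calculation and the sachet using the same granola weight. If they do not, part of any between-arm difference in weight loss would reflect a difference in calories rather than satiety. A reader also cannot reproduce the intervention from the article.

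The breakfast is a lesser matter. Its protein target is expressed against two different denominators and nothing ties them together, yet missing the high-protein breakfast forms part of a rule that removes participants from the study.

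**Working it through.** **1. Granola weight.** Inputs are the section 2.11 recipe and the Table 1 sachet.

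- Base: 30 + 24 + 15 + 5 = 74 g
- Salty: 74 + 0.15 + 0.3 = 74.45 g
- Sweet: 74 + 5 + 10 = 89 g
- Table 1: 30 g. Ratios: 74/30 = 2.5 and 89/30 = 3.0

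**2. Can 30 g be reproduced?** Readings tried:

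- Half of a serving, since the sachet may be split in two: 37 g (base), 37.2 g (salty), 44.5 g (sweet).
- Cashew nuts outside the sachet: 74 − 15 = 59 g (base) to 89 − 15 = 74 g (sweet) must still fit in 30 g.
- Cashew nuts inside the sachet: 30 − 15 = 15 g is left for 59 g of oats, seeds and oil.
- Table 1 as sachet plus cashews: 30 + 15 = 45 g, still short of 74 g.

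None gives 30 g. The oats alone weigh 30 g, but the table does not label the figure as oats.

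**3. Energy at stake.** The article gives no energy density, so 4–5.5 kcal/g is assumed. Gap = (recipe weight − Table 1 weight) × kcal/g, compared with 500 kcal.

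| Table 1 read as | Salty, 74.45 g | Sweet, 89 g |
|---|---|---|
| 30 g | 44.45 g: 178–244 kcal (36–49%) | 59 g: 236–325 kcal (47–65%) |
| 30 g + 15 g cashew = 45 g | 29.45 g: 118–162 kcal (24–32%) | 44 g: 176–242 kcal (35–48%) |

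Across both readings and flavours the range is about 120–325 kcal/day, or 24–65% of the planned deficit. The direction depends on which weight is in the menus and which is in the sachet.

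**4. Breakfast protein.** Let E be daily energy, b breakfast's share of E, and p the diet's protein share of energy (0.20–0.25, Table 1). At 4 kcal per gram of protein:

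- Section 2.11: 0.20 × b × E / 4
- Table 1: 0.20 × p × E / 4

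These are equal only when b = p, that is, when breakfast supplies 20–25% of daily energy. The menus have six meals a day (section 2.10), and b is not stated. With E assumed to be 1,500 kcal:

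- Table 1: 0.20 × 0.20 × 1500 / 4 = 15.0 g, to 0.20 × 0.25 × 1500 / 4 = 18.8 g
- Section 2.11: 7.5 g at b = 10%, 12.5 g at one sixth, 15.0 g at 20%, 18.8 g at 25%, 22.5 g at 30%

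**The case against.** The strongest reply is that the harm is conditional. Menus are calculated in a spreadsheet from food-composition tables (section 2.10), the itemised recipe is enough to compute energy, and Table 1 is only an overview. Nothing shows that the spreadsheet uses 30 g, and the figure could be a labelling slip for the oats. This stands as far as it goes. A reader might infer that the arms do have unequal restriction, but the article supports only that they would if the two weights were mixed. The reply does not remove the contradiction: the article states both amounts, and a slip still has to be corrected.

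It is also fair that a gap measured only against 30 g would ignore the possible 45 g reading of Table 1. The range above includes it.

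Some further inferences are tempting but not supported:

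- *The two breakfast figures are incompatible.* They have different denominators, and both hold if breakfast supplies 20–25% of energy. The target is loosely fixed, not contradictory.
- *The discontinuation rule fails for granola.* It rests on absence of consumption, and adherence is checked by empty packages. Neither uses grams, so the granola part works at any sachet weight.
- *The breakfast is not high in protein because 20% is the bottom of the arm's all-day range.* The article never claims that breakfast exceeds the rest of the day. Table 1 sets its contrast against control.
- *Listing meal frequency as a satiety strategy contradicts the shared meal division.* Advice on keeping to a meal pattern can accompany the same menus.

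**Conclusion.** The granola amount is wrong as written: section 2.11 and Table 1 cannot both be right, and the separate cashew row does not reconcile them. The weights (74, 74.45 and 89 g against 30 g) are exact and need no assumption. The possible energy difference of about 120–325 kcal/day, or 24–65% of the 500 kcal deficit, rests on an assumed 4–5.5 kcal/g and on menus and sachets using different weights, which the article neither shows nor excludes. If they already agree, correcting the text is enough.

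The breakfast is a secondary clarification. It has two definitions that coincide only at an unstated breakfast share, so the breakfast part of the discontinuation rule has two possible targets. The gram figures there assume 1,500 kcal/day. Sample size and power are not affected.

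**What to change.** Reconcile section 2.11 with Table 1 so that both state:

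- one sachet weight for each flavour;
- whether the 15 g/day of cashew nuts is inside the sachet or additional to it;
- one definition of the high-protein breakfast, also used in the section 2.13 discontinuation rule.

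Then check that the menu spreadsheet uses the granola weight actually supplied, so that both arms carry the same calculated restriction. Which values apply is for the sponsor to decide. The cost is protocol wording and a spreadsheet check, with no added participants, visits or procedures.

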### Collective intervention

2.12

In addition to the nutritional intervention, participants in both groups (control and intervention) will receive a continuous collective intervention consisting of eight meetings (the first six biweekly and the last two monthly), conducted by psychologists and nutritionists throughout the 18 weeks of the study. The collective intervention will follow Carl Rogers' person‐centred approach. From this perspective, facilitators will create a welcoming, judgement‐free environment that stimulates self‐awareness through reflection and careful clarification of doubts without offering direct advice. The principle is that, as participants broaden their understanding of themselves, viable solutions to their challenges emerge autonomously.^28^, ^29^

### Monitoring and adherence to study protocol

2.13

Adherence to the protocol (in both the control and intervention groups) will be monitored through seven nutritional counselling consultations conducted biweekly during the first 2 months and subsequently monthly until the completion of the 18‐week study. The consultations will be conducted in person or via video conference, during which the consumption of granola, any possible adverse events, and the introduction or changes in usual medication doses for acute or continuous use will be recorded, and nutritional guidelines will be reinforced. In addition, during individual dietary consultations, adherence to granola consumption will be assessed by counting the returned empty packaging.

The control groups will also attend the monitoring visits and will undergo the same assessments as the intervention groups. During the study period, participants who do not adhere to the eating plan (in both the control and intervention groups), do not have good adherence to the satiety protocol (absence of consumption of the granola and intake of the high‐protein breakfast on at least five consecutive days), have a frequency of less than 75% in the activities of the collective intervention and nutritional consultations, or who experience any non‐transient adverse event and gastrointestinal symptoms that compromise health or quality of life related to the consumption of granola, will be discontinued from the study.

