### Eligibility criteria

2.3

The study's inclusion criteria comprise: men and women aged 20–55 years who are overweight (BMI 27.0–29.9 kg/m^2^), have an elevated waist circumference (≥80 cm for women and ≥90 cm for men), and excess body fat (>30% for women and >20% for men), associated with at least one of the other components of the metabolic syndrome.^17^ Individuals with obesity (BMI ≥30 kg/m^2^) are also included if they present an elevated waist circumference and excess body fat, regardless of the other components.

The exclusion criteria are: women who are pregnant, breastfeeding, menopausal or with self‐declared intention to become pregnant during the trial; athletes; shift workers; clinical diagnosis of any mental, physical and/or intellectual disorder; food intolerances or allergies to the test products; type 1 diabetes mellitus; self‐report history of autoimmune diseases or use of immunosuppressant drugs; hormonal, digestive, inflammatory bowel, liver, kidney, pancreatic, cardiovascular or heart diseases; eating disorders; cancer; infectious episode within the past month; history of illicit drug use and/or alcohol intake >210 and >140 g of ethanol/week for men and women, respectively; planned or recent bariatric surgery; self‐reported weight fluctuations (5% of usual weight) in the past 3 months; habitual consumption of granola, nuts, whole grains or seeds (sesame, pumpkin and sunflower seeds, flaxseed) >30 g/day; adherence to vegan, vegetarian or dietary restriction diet (gluten and lactose); consumption of appetite and energy metabolism altering medications; use of vitamins, minerals and omega‐3 supplements above the Dietary Reference Intakes; use of fibre supplements (psyllium and inulin); adherence to a restrictive or therapeutic diet in the past 3 months; and current and anticipated enrolment in another research study.

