### Data handling and quality

2.27

The entire team involved in collecting data for this study will receive specific training and have prior experience in the field. The study's progress, protocol compliance, data validity and integrity and ethical considerations will be periodically assessed by a clinical trial monitor. Participants will be instructed to answer questions truthfully. An intention‐to‐treat (ITT) analysis will be used to include data from individuals who withdraw from the study for any reason. All participants will be followed for 18 weeks after treatment assignment.

After the questionnaires are administered, the responses will be checked for completeness and consistency. To ensure accurate data entry, two operators will enter the data independently, and the data entry system will feature pre‐programmed logic check functions to minimise transcription errors.

A unique numeric code will identify each participant. All data will be archived at the institution and accessible exclusively to the research team. Information from the questionnaires and consent forms will be kept in printed format, stored separately from other study data and identified by a specific numeric code.

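### Section 2.13 removes participants from the study on grounds that partly apply to one diet arm only, while Section 2.27 promises 18-week follow-up of everyone and an ITT analysis

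*Protocol article*

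**What the plan says.** Section 2.13 (Monitoring and adherence to study protocol) puts four grounds for removal in one sentence:

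- not following the eating plan, in either arm;
- those who "do not have good adherence to the satiety protocol (absence of consumption of the granola", where the parenthesis goes on to the high-protein breakfast and a run of at least five days;
- attendance below 75% at the group sessions and consultations;
- a non-transient "adverse event and gastrointestinal symptoms that compromise health or quality of life related to the consumption of granola, will be discontinued from the study".

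The verb at the end governs all four, and what is discontinued is participation in the study, not the granola or the diet. The same section says of the controls: "The control groups will also attend the monitoring visits and will undergo the same assessments as the intervention groups".

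Section 2.27 (Data handling and quality) says that an ITT analysis "will be used to include data from individuals who withdraw from the study for any reason", and then: "All participants will be followed for 18 weeks after treatment assignment".

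Only the satiety arm is given granola. Table 1 instructs controls as follows: "Avoid consuming granola, oats, pumpkin, sunflower, flax and sesame seeds". Table 2 schedules the GSRS and the Bristol Scale at baseline, week 12 and week 18.

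**The concern.** A site team cannot obey both sections. Under Section 2.13 a participant with persistent symptoms leaves. Under Section 2.27 the same participant is followed to week 18. If Section 2.13 is what happens in practice, someone removed before week 12 has no post-baseline scores, and someone removed between weeks 12 and 18 lacks the last.

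The loss need not be even. The satiety-protocol ground has no counterpart in the control arm. The symptom ground, if it is tied to granola, has none either, and there the reason for removal is the very thing the GSRS scores. A small or absent GSRS difference between the diets could then partly reflect the absence of those who tolerated granola badly.

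**Working it through.** **Comparing the sections.** The firm clash is between removal from the study (2.13) and 18-week follow-up of all (2.27). The ITT sentence clashes less sharply: it foresees withdrawals and says their data count, but that helps only if later data exist. No section says that discontinued participants still attend assessments.

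**Inputs.** There are 30 per group and two genetic-risk groups per diet, so 60 per diet arm. The planned 30% loss leaves 60 × 0.70 = 42. The plan states no removal rate and no GSRS effect, so there is no figure of its own to reproduce. Two quantities are assumed: the share p of the satiety arm removed for symptoms before a visit (5% or 10%, that is 3 or 6 of 60), and the gap d between the GSRS scores of those removed and those remaining (1 to 2 SD).

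**Shift if those removed are not scored.** The full-arm mean exceeds the mean of those remaining by p × d.

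- p = 0.05: 0.05 × 1 = 0.05 SD to 0.05 × 2 = 0.10 SD.
- p = 0.10: 0.10 × 1 = 0.10 SD to 0.10 × 2 = 0.20 SD.

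These are not strict bounds, since d = 2 is a chosen limit. A second model removes people by a propensity that correlates 0.6 to 1.0 with a normal GSRS score. It gives 0.07-0.11 SD at 5% and 0.12-0.20 SD at 10%, in the same direction.

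**Partial recovery.** Suppose a fraction f of those removed is scored and a fraction r of the symptom rise remains. The shift is p·d − p·f·r·d / (1 − p + p·f). With f = r = 0.5 and d = 1:

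- p = 0.05: 0.05 − 0.0125/0.975 = 0.037 SD; twice that, 0.074, at d = 2.
- p = 0.10: 0.10 − 0.025/0.95 = 0.074 SD; 0.147 at d = 2.

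With f = r = 1 the shift is zero.

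**If controls are removed too.** The shift is (p1 − p0) × d. For 5% v 2% it is 0.03-0.06 SD; for 10% v 5% it is 0.05-0.10 SD.

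**Against sampling error.** The standard error of the arm difference is √(2/n): √(2/60) = 0.183 SD and √(2/42) = 0.218 SD. With k the ratio of shift to standard error, the coverage of a nominal 95% interval is Φ(1.96 − k) − Φ(−1.96 − k).

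| Removed | n per arm | k | Coverage |
|---|---|---|---|
| 5% | 60 | 0.27-0.55 | 94.1-91.5% |
| 5% | 42 | 0.23-0.46 | 94.4-92.6% |
| 10% | 60 | 0.55-1.10 | 91.5-80.5% |
| 10% | 42 | 0.46-0.92 | 92.6-85.0% |

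**The case against.** Discontinuation from the study may be loose wording for leaving the programme, with follow-up continuing as Section 2.27 says. That reading is possible, but the article does not state it, so the clash over follow-up stands. It would be too strong to say that Section 2.27 flatly contradicts Section 2.13 on ITT.

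A reader might infer that the ANOVAs in Section 2.28 drop everyone without a score. Section 2.28 does not say so, and handling of missing values may sit in a document not shown. The GSRS shift is therefore conditional.

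The symptom clause is ambiguous. If any non-transient adverse event suffices, controls can be removed too and the shift falls as shown. Eligibility also excludes digestive disease and people with "food intolerances or allergies to the test products", so few may be affected.

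The GSRS is not a headline outcome. The list in Section 2.6 opens "Secondary outcomes will include improvements in indicators of quality of life" and does not name gut health, which appears only as a Table 2 measure. No tolerability hypothesis is planned.

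A further temptation is to say that adverse events would go unrecorded in step with removal. On this ground the event causes the removal, so it is already known to the trial, and adverse events are recorded at consultations in both arms. Nor is it certain that stopping granola alone triggers the five-day rule: the text can be read as requiring that both the granola and the high-protein breakfast are missed.

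**Conclusion.** The conflict holds for every ground in the Section 2.13 sentence, and it is firmest against the promise of 18-week follow-up. Removal can differ by arm through the satiety-protocol ground and, if it is tied to granola, the symptom ground.

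The effect on the GSRS is a conditional risk, not an established bias. It arises if those removed are not assessed and their scores are not otherwise recovered. It favours the satiety arm by roughly 0.05-0.1 SD at an assumed 5% removed and 0.1-0.2 SD at an assumed 10%, and by less if controls are removed as well. The direction does not carry over to the Bristol Scale, which grades stool form and is abnormal at both ends. A reader might also infer a biased weight result. The adherence and attendance grounds could bear on weight, but nothing here shows a direction or size for it.

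Severity is minor. Confidence is medium, because the rates are unknown and the clause is ambiguous.

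**What to change.** In Section 2.13, replace removal from the study by stopping the granola or the assigned diet, as applicable. State that these participants still attend the week-12 and week-18 assessments and have adverse events recorded to week 18. Apply this to all four grounds, so that someone who stops granola for symptoms is not then removed under the adherence rule.

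The cost is a few lines of text. Section 2.27 already promises the follow-up, and consultations may be held by video. The downsides are that some participants will not attend, that GSRS scores taken after granola has stopped may show eased symptoms, and that results may look slightly less favourable.

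A table of gastrointestinal events by diet arm in all randomised participants would be a useful but optional addition.

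### Section 2.13 removes non-adherent participants from the study, on grounds that fall more heavily on the satiety arm, while section 2.27 promises 18 weeks of follow-up and an ITT analysis for everyone

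*Protocol article*

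**What the plan says.** Section 2.13 (Monitoring and adherence to study protocol) gives these grounds for removal:

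- not keeping to the eating plan, expressly in both arms;
- participants who "do not have good adherence to the satiety protocol", defined by granola and high-protein breakfast intake over at least five consecutive days;
- participants who "have a frequency of less than 75% in the activities of the collective intervention and nutritional consultations";
- participants with a non-transient adverse event and gastrointestinal symptoms harmful to health or quality of life "related to the consumption of granola, will be discontinued from the study".

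The consequence is leaving the study, not only stopping the diet or the granola.

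Section 2.27 (Data handling and quality) says that an ITT "analysis will be used to include data from individuals who withdraw from the study for any reason". It adds: "All participants will be followed for 18 weeks after treatment assignment".

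Three other places matter. Table 1 tells controls to avoid granola, and section 2.11 gives the satiety protocol to the intervention group only. Table 2 lists weight loss as an outcome at weeks 12 and 18. Section 2.28 plans a mixed ANOVA over baseline, week 12 and week 18.

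**The concern.** A participant taken out of the study before week 18 is not followed for 18 weeks, so a team that applies section 2.13 cannot also deliver the follow-up in section 2.27. The loss would be created by the protocol itself, through removal by the investigators and not through participants choosing to leave. A weight that was never measured cannot be recovered by any later analysis.

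Adherence, attendance and tolerability all arise after randomisation, and adherence is plausibly related to weight loss. If removal follows them, and follows them under more rules in one arm, those left at week 18 are no longer the groups that were randomised. The contrast affected is control versus satiety diet on the primary outcome.

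**Working it through.** **Step 1. Set the two rules side by side.** Section 2.13: a participant who meets a ground leaves the study. Section 2.27: every participant is followed for 18 weeks. They could be reconciled only by a statement that removed participants still attend the assessments, and the article has none.

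**Step 2. What data are lost.** Removed before week 12: no post-baseline weight. Removed between weeks 12 and 18: a week-12 weight but no week-18 weight. A classical mixed ANOVA over three visits needs all three values, or a rule for filling them in.

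**Step 3. Which grounds reach which arm.**

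| Ground in 2.13 | Control | Satiety |
|---|---|---|
| Eating plan | yes | yes |
| Attendance under 75% | yes | yes |
| Satiety protocol | no | yes |
| Granola-related event or symptom | no, on the natural reading | yes |

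**Step 4. How large a bias could follow.** The documents give no removal rates by arm, no SD and no link between adherence and weight loss, so these are assumptions.

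- From section 2.7: 120 participants, hence 60 per diet arm, and 30% loss (36 people).
- Assumed: SD of percentage weight change 4.5 points; correlation r of 0.3 or 0.5 between adherence and weight loss; no true diet effect.
- Assumed split of the 36 removals: 12 control and 24 satiety (20% vs 40%), or 15 and 21 (25% vs 35%).

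Suppose adherence is standard normal and the lowest fraction p is removed. The mean adherence of those remaining is m(p) = φ(z_p)/(1 − p), where z_p is the p-quantile and φ the normal density. The spurious difference among those remaining is r × SD × [m(p_satiety) − m(p_control)].

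- 20% vs 40%: m = 0.350 and 0.644, difference 0.294. Bias = 0.3 × 4.5 × 0.294 = **0.40** points, or 0.5 × 4.5 × 0.294 = **0.66** points, in favour of satiety.
- 25% vs 35%: m = 0.424 and 0.570, difference 0.146. Bias = **0.20** or **0.33** points.
- Equal removal, or r = 0: bias **zero**.

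In 20,000 simulated trials with no diet effect, a t-test on those remaining at nominal 5% rejected about 7% of the time (r = 0.3) and 11% (r = 0.5) for 20% vs 40%. For 25% vs 35% the rates were about 6% and 7%.

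**Step 5. The same removals under another analysis.** Suppose removed participants are kept in the analysis at zero weight change, and the true mean loss is μ in both arms. The arm mean is then (1 − p)μ + r × SD × φ(z_p). Take 20% vs 40% and an assumed μ = 5%:

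- r = 0.3: control 0.8 × 5 + 1.35 × 0.280 = 4.38; satiety 0.6 × 5 + 1.35 × 0.386 = 3.52; **0.86** points against satiety.
- r = 0.5: control 4.63; satiety 3.87; **0.76** points against satiety.

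At μ = 3% the difference is 0.46 or 0.36 points against satiety. The sign therefore depends on how the missing weights are handled.

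**The case against.** The strongest reply is that section 2.27 already commits to ITT with data from those who withdraw, and that the handling of missing weights belongs in an analysis plan that is not shown. In part this stands. The ITT sentence can be met in form with whatever was collected before removal, so the firm contradiction is with the 18-week follow-up sentence. But an analysis plan can only choose how to fill a gap; it cannot restore the weight.

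A reader might infer that the rule is bound to flatter the satiety diet. The documents do not support that. The direction depends on an unstated analysis choice (steps 4 and 5). It also depends on whether those removed would have lost less weight, and participants removed for gastrointestinal symptoms might have lost more. Nor does the article support a doubled removal rate in the satiety arm: it gives only 30% overall, and nothing shows how often the five-day ground would be met.

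A reader might also infer that both of the last two grounds in the table are strictly confined to the satiety arm. Only the satiety-protocol ground is beyond dispute. In the adverse-event clause, the granola qualifier could attach to the gastrointestinal symptoms alone, so that another adverse event might remove a control. The natural reading ties the whole clause to granola, but it is a reading.

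Finally, it is tempting to say that removal hides poor tolerability. Section 2.13 records adverse events at the consultations in both arms, and removals can be reported by arm and reason. What is lost is the later outcome data of those people.

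**Conclusion.** The point holds as a contradiction and a risk of bias. With high confidence: sections 2.13 and 2.27 cannot both be carried out as written, following 2.13 loses primary-outcome data for reasons that arise after randomisation, and at least one removal ground exists in one arm only.

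The size and direction of any bias are conditional. The figures in step 4 hold only for an analysis of those remaining, with poorer outcomes among those removed, and with the assumed rates, SD and correlations. They are illustrations, not estimates for this trial. The contradiction does not depend on them. It should be settled while weights can still be collected.

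**What to change.** Reconcile section 2.13 with section 2.27 by separating two events: stopping the assigned diet or granola, and leaving the study. When to stop the diet or granola stays with the investigator, and no rule for that is proposed here.

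State that participants who meet a section 2.13 criterion keep the week-12 and week-18 assessments, at least body weight, unless they withdraw consent, and that they are analysed in the arm to which they were assigned. If the adherence thresholds are kept for analysis, use them only to define a secondary per-protocol analysis. Report stops and withdrawals by arm and reason.

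The cost is a change of wording plus the visits retained. If all 36 participants in the 30% allowance were removed under section 2.13 before week 12, that would be at most 36 × 2 = 72 visits. Section 2.27 already promises every one of them.
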